**Fig. 9 Fig9:**
[figure not shown]
Power analysis based on our baseline sample size (600) and effects observed in our pilot analyses: A strong association between mind wandering and variability (*r* = -0.53), a moderate association between variability and ADHD (*r* = 0.39), and a small to moderate association between variability and inattention (median *r* = 0.24)

Our sample size of 600 children consists of children tested in schools and on an individual basis at home. By including participants that are recruited individually and tested at home, we add a new variable of a situational context. This enables us to test potential differences in cognitive variability between school and home environments. Factors such as systematic differences, the role of self-initiating sessions, the absence of peer influence, and variations in noise levels between both contexts are likely to have distinct impacts on cognitive variability. To ensure sufficient power for each group, we hope to recruit at least 135 participants tested at home, allowing us to both ensure precision of parameter estimation within each group (home and school based), as well as detect the hypothesised effect size group difference between the two with > 80% certainty (see Fig. 10).

**Fig. 10 Fig10:**
[figure not shown]
Power analysis based on the lowest sample size per subgroup (135) to detect effects observed in our pilot analyses at minimum 80% power

Parallel to this, to understand the processes related to variability in children, our study considers various potential variables underlying cognitive variability (i.e., neural, psycho-social, cognitive, genetic). Our goal is to determine how each variable influences variability and to detect individual differences in this regard. Therefore, it is important not only to consider variables as unique predictors to variability but also to account for potential different subgroups of participants. Individuals are likely to belong to distinct classes or groups for whom variability is potentially more affected by certain variables, such as sleep or mood, while others may not exhibit the same impact. Consequently, we aim to explore different variability profiles among individuals, each characterised by unique underlying patterns. Therefore, our sample of 600 is divided based on the identified profiles. To ensure sufficient power for each group, we aim for the smallest subgroup size to be around 135 participants, allowing us to detect our expected effect sizes with 80% certainty (see Fig. 10). This enables us to investigate whether the overall sample can be considered a mixture of different distributions arising from distinguishable subgroups in the population with different underlying processes.

#### Imaging arm

For the smaller imaging subsample the CODEC study has > 80% power to detect modest (0.2) associations and at > 99% power to detect moderate (*r* = 0.3) effects, see Fig. 11. This is sufficient to detect the expected moderate effects in line with previous findings (between neural data - Fractional Anisotropy (FA) and variability = 0.34; [68]).

**Fig. 11 Fig11:**
[figure not shown]
Power analysis to detect continuous effects in the imaging subsample of 200 participants

## Discussion

Children’s cognitive performance fluctuates across temporal resolutions, and these fluctuations are known as within-subject cognitive variability. Cognitive variability could act as a potential early predictor of neurodevelopmental disorders [20, 21]. Despite the potential importance of cognitive variability, multiple factors including a lack of appropriate quantitative techniques and the unavailability of sufficiently rich datasets (including estimates across various tasks and temporal resolutions), cognitive variability, its underlying mechanisms and long-term implications are relatively neglected in the current literature.

The CODEC study addresses these remaining gaps by combining an accelerated longitudinal design including a behavioural ‘burst’ measurement (3 times per day, 5 days per week) and deep phenotyping, including fMRI, eye-tracking and a set of questionnaires, with advanced statistical methodologies. 600 children (age 7–12 at first measurement) are followed for up to 3 years as they undergo rapid cognitive development. Each year consists of a ‘burst’ week of experience sampling assessments of five cognitive domains (reasoning, working memory, processing speed, vocabulary, exploration), sleep quality, mood, and background noise, conducted both in classrooms and home settings. Academic outcomes and task preference are also collected once a year. A subset of 200 children of the CODEC participants take part in the deep phenotyping sessions (CODEC-MRI), once at the start of the study, in year 1, and once at the end in year 3. In addition to the cognitive battery, the deep phenotyping session consists of structural and functional MRI, eye-tracking, parental measurements (on the cognitive battery) and questionnaire-based demographic and psychosocial measures as reported by parents and children. Analysing the data through Dynamic Structural Equation Modelling, allows us to simultaneously capture variability and the multilevel structure of trials nested in sessions, days, children and classrooms. In doing so, we aim to pave the way to a better understanding of cognitive variability and its implications, providing insight into the mechanisms and consequences.

In line with the open-data principles, the data generated by the CODEC study will be made openly available for scientific reuse to be shared with fellow researchers when data can be shared securely. There is no cost attached to the reuse of the data. Data sharing is done using the Radboud research data repository [127] in accordance with institutional, Radboud University, and EU guidelines. We share only anonymised behavioural data, and anonymised (derived) (f)MRI data.

The findings of this study lead to insight in three main areas: (1) the reliable measurement of individual differences in variability, (2) the underlying predictors and potential causes, and (3) the long-term trajectories and consequences of cognitive fluctuations. In conclusion, the CODEC study aims to provide valuable insights into the mechanisms, consequences, and potential interventions related to cognitive variability, ultimately contributing to more equitable assessments and improved support for young individuals with variable cognitive performance.

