### Study procedures and assessments

#### Behavioural procedure – school recruitment

Initial ‘burst’ week - The CODEC team organises an initial visit to the schools with the relevant teachers and hands out tablets to the children. All children perform the same tasks, but no data is collected for children for whom consent was not given. Children perform the tasks in the classroom, independently but in a group setting, for 2–3 times a day for the duration of a week using the same tablet, supported by teachers in the classroom. The precise timing of the measurement occasions is determined in collaboration with the teacher, to accommodate the school’s schedule, and thus will vary between classrooms. The first testing session will be assisted by a member(s) of the CODEC team to ensure that all task demands are clear, and any logistical (e.g., login) problems can be addressed immediately. Children have the opportunity to ask questions, and tick a box prior to starting the first testing session indicating that they have understood all instructions. In each testing session, three of the five tasks (selected pseudorandomly) are played by the child for the duration of 5 min (15 min in total) to make sure that the session remains sufficiently short and exciting for the children.

Follow-up measurement occasions - Throughout each year of testing, up to two additional testing occasions can be planned in agreement with the teachers. On these occasions, the procedure is identical, but all five cognitive tasks are performed once in a single session. Two follow-up ‘burst’ weeks take place after approximately one (in the second year of the study) and 2 years (in the final year of the study), for which the procedure is identical to the initial ‘burst’ week.

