Additionally, we study the role of psychological (e.g., mind wandering, sleep, mood) and environmental (e.g., socio-economic status (SES)) factors on between- and within-person differences in variability by using them as predictors in a (regularised) SEM.*Hypothesis 2.8: Individuals from lower SES backgrounds will show greater day-to-day variability.**Hypothesis 2.9: Individuals with greater mind wandering tendency will show greater cognitive variability, especially at the trial-to-trial level.**Hypothesis 2.10: Days or testing sessions with greater negative affect, poorer sleep, and/or more background noise will be days or testing sessions with greater variability as well as poorer mean performance.**Hypothesis 2.11: Tasks ranked as less enjoyable (individually) will be tasks with greater variability as well as poorer mean performance (when adjusting for task difficulty).*

To understand variability within individuals, we have to consider not only unique within-subject predictors but also potential subgroup differences. Neubauer et al. [43], identified subgroups of different profiles within a population for whom mood had varying effects on variability (i.e., low mood leading to higher variability, high mood leading to higher variability, mood having little effect on variability, and a group where both low and high mood lead to higher variability). We will use mixture models to identify subgroups within the population, allowing for the coupling of variability with factors like mood, sleep, background noise, and motivation (task rank). Specific subgroups that will be identified due to interactions between these factors are mostly exploratory, as not enough research has investigated this question so far.*Hypothesis 2.12 (exploratory): The overall sample will consist of a mixture of distinguishable subgroups in the population with a subgroup having a negative impact of mood, sleep quality, background noise, and motivation (task ranking) on variability and a subgroup having no negative impact of mood, sleep, background noise, and motivation (task ranking) on variability.*

The parents or guardians of the subgroup taking part in the imaging study are also asked to perform the cognitive tasks on tablet at each session. These scores act as predicting variables in latent mixed models to explore possible hereditary correlations.*Hypothesis 2.13: Variability will be correlated between parents and children*

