### Sample size considerations

#### Behavioural arm

The number of subjects needed in DSEMs have previously been examined through a series of Monte Carlo simulations [126]. Focusing on univariate two-level autoregressive models, they demonstrate that the DSEM performs well across a range of scenarios. For example, the estimation stability gained from a larger number of subjects is greater than the benefits of a large number of trials. Crucially, they demonstrate that DSEM achieves a highly reliable estimate of individual differences in trial-to-trial cognitive variability with anywhere upwards of 15 trials, given 200 subjects (average estimate over 500 repetitions/true value = 0.88, [126]).

In terms of power to detect significant associations, the behavioural arm of the CODEC study is effectively at ceiling (see Fig. 9) for effect sizes we observe in previous literature, including the effect of mind wandering on variability (*r* = -0.53, 100% power; [52]), variability on ADHD symptoms (*r* = 0.39, 100%; [94]), and inattention on variability (*r* = 0.24, 100% power; [19]). For the full behavioural sample (*N* = 600), even small effect sizes (*r* = 0.11) can be detected with 80% power.

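### School sessions are shared by a whole class, so a literal nested model can make the H2.10 noise test too liberal; the power figure for r = 0.11 also makes no allowance for classrooms

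*Protocol article*

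**What the plan says.** The Discussion, and in almost the same words the Method part of the Abstract, says the models will "simultaneously capture variability and the multilevel structure of trials nested in sessions, days, children and classrooms". A classroom level is therefore planned.

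Under Behavioural procedure – school recruitment, the article states: "Children perform the tasks in the classroom, independently but in a group setting". The same section has session times agreed with each teacher, so they differ between classes but are common within one. Study design presents centrally organised sessions and the measurement of classroom noise as two of three benefits of school testing. The Cognitive tasks section has ambient decibels recorded at the start and end of every session.

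Hypothesis 2.10 (Key hypotheses) predicts: "Days or testing sessions with greater negative affect, poorer sleep, and/or more background noise will be days or testing sessions with greater variability", together with poorer mean performance.

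On sample size, the Behavioural arm section supports the number of subjects with a cited simulation study: "Focusing on univariate two-level autoregressive models, they demonstrate that the DSEM performs well across a range of scenarios". It then says of the full sample that "even small effect sizes (*r* = 0.11) can be detected with 80% power". No significance level, class size, intraclass correlation (ICC) or design effect is given.

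**The concern.** A nested list in which sessions and days sit below children implies that each child has his or her own sessions, unrelated to those of classmates. In a classroom, one session is a single event for everyone present: the same time of day, the same preceding lesson, the same interruptions and largely the same noise reading. A classroom intercept absorbs stable differences between classes, but not something that happens to one class in one session.

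This matters most when the predictor is also shared. For noise, much of the information comes from the number of class-sessions, not child-sessions. If the model counts child-sessions as independent, the interval for noise is too narrow, and a chance link between noisy sessions and poor sessions can be declared real. Noise in the classroom is one of the stated reasons for testing in schools, so this is not a peripheral analysis.

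The power statement raises a related question. Schools are the core recruitment route and the analysis has a classroom level, yet the smallest detectable correlation is given without any allowance for classrooms.

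**Working it through.** **1. Reproducing the stated power.** The significance level is not stated; two-sided 5% is assumed. With Fisher's z, power = Φ(atanh(r)·√(N−3) − 1.96).

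- The same formula recovers the article's other figures. For N = 200 it gives 81.2% at r = 0.2 and 99.1% at r = 0.3, against the stated "> 80% power to detect modest (0.2) associations and at > 99% power to detect moderate". For N = 135 and r = 0.24 it gives 80.3%, against 80%.
- For N = 600, the smallest r with 80% power is tanh((1.960 + 0.842)/√597) = 0.114, which prints as 0.11.
- At r = 0.11 exactly, power is 77.0%.

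The stated figure is therefore the independent-children result, rounded to two decimals.

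**2. Allowing for classrooms.** The article hopes for at least 135 children tested at home, which leaves at most 600 − 135 = 465 in classes. Assumptions not in the document: 20 participating pupils per class, outcome ICC 0.05–0.10 and predictor ICC 0.1–0.3. For a correlation between two child-level variables, the design effect is 1 + (m−1)·ICCx·ICCy, applied to the classroom children only.

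| | Lower ICCs | Higher ICCs |
|---|---|---|
| Design effect | 1 + 19×0.1×0.05 = 1.095 | 1 + 19×0.3×0.10 = 1.57 |
| Effective N | 465/1.095 + 135 ≈ 560 | 465/1.57 + 135 ≈ 431 |
| Detectable r, 80% power | 0.118 | 0.135 |
| Power at r = 0.11 | 74% | 63% |

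For a predictor that is constant within a class, the design effect is the larger 1 + (m−1)·ICC. With the same 465/135 split, power at r = 0.11 is then 67%, 57% and 47% at an outcome ICC of 0.02, 0.05 and 0.10.

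The larger effects hold up. Even with all 600 children in classes of 20 and the larger design effect, power at r = 0.24 is 94% or more up to an ICC of 0.10. It falls below 80% (to 79%) only at 25 per class and an ICC of 0.15.

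**3. The noise test in H2.10.** Assumed layout: 23 classes × 20 pupils (460, close to the 465 above) × 13 sessions, within the 10 to 15 that two to three sessions a day for five days allow. The outcome is one score per child and session, centred on the child so that stable class and child differences are removed. There is no true noise effect. Noise is taken as half to fully shared within the room. The naive test treats child-sessions as independent.

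As a check, the variance of the noise slope is understated by about DE = 1 + 19 × (class-session share of outcome variance) × (shared fraction of noise), and the false-positive rate is 2·(1 − Φ(1.96/√DE)).

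| Class-session share | DE, noise half / fully shared | Formula | Simulation |
|---|---|---|---|
| 0 | 1.00 / 1.00 | 5% | about 5% |
| 0.02 | 1.19 / 1.38 | 7–10% | 8–9% |
| 0.05 | 1.48 / 1.95 | 11–16% | 11–15% |
| 0.10 | 1.95 / 2.90 | 16–25% | 16–24% |

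Repeat simulations differ from these by a point or two. Classroom-clustered standard errors return the rate to about 4–6% throughout.

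**The case against.** Three stronger readings are tempting, and the documents support none of them.

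- *The 80% is wrong because r = 0.11 gives 77%.* The detectable value is 0.114, printed to two decimals. That is rounding, and it has nothing to do with classrooms.
- *Classroom clustering is ignored in the analysis.* It is not: classrooms are named as a level. What is missing is a stated term for the session a class shares, and an allowance in the power figure.
- *The H2.10 noise findings will be inflated.* The article gives one summary sentence on nesting and says elsewhere that such factors enter a possibly regularised structural equation model. The random-effects structure for H2.10 is not given, the preregistered analyses are not shown, and the summary sentence could be loose wording for a cross-classified model. Nothing rules out clustered inference. The inflation also depends on a variance share that the article does not state, and at zero there is none.

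It is also fair to say that H2.10 covers mood and sleep, which each child rates individually. Those tests are exposed only as far as the ratings move together within a class. The r = 0.11 sentence, finally, is an illustration; the effects the article expects are r = 0.24 to 0.53.

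What stands is that the structure is stated twice, that taken literally it does not match how school sessions are run, and that the power figure is given as a number on an independence assumption which the plan's own classroom level does not share.

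**Conclusion.** The point holds in conditional form. If the stated nesting is fitted literally, the noise test in H2.10 has no protection against disturbances shared by a class-session. Its false-positive rate then rises from about 5% to 8–9%, 11–15% or 16–24% as the shared variance goes from 0 to 0.02, 0.05 or 0.10. These figures rest on an assumed number of classes, class size and number of sessions, on noise being half to fully shared in the room, and on a session-level score standing in for the full dynamic model. They apply to the school sample only.

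The 80% power at r = 0.11 is correct to rounding for independent children and optimistic for this design: about 74–63% under the assumed class size and ICCs, with a detectable r of about 0.118–0.135. The statement that power is effectively at ceiling for the effects from earlier work is largely unaffected.

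**What to change.** For H2.10 in the school sample, state that sessions are crossed with children within classrooms. Either add a classroom-by-session random effect (a cross-classified model) or base the intervals for noise on classroom-clustered standard errors. Enter noise as two terms: the class-session mean and the child's deviation from that mean. Home-tested children need no such term.

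In the Behavioural arm section, give the detectable correlation as 0.114 for independent children. Beside it, give the value with a design effect for the classroom-recruited children, stating the assumed class size and ICCs.

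The cost is one extra random effect or a different standard error, wider intervals for noise, and one restated figure. No data collection changes.

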## Data Availability

The anonymised datasets generated during this study will be made openly available to researchers for scientific reuse that is not limited to the research project for which the data was initially collected, after completion of data collection and cleaning. There will be no cost for reusing the data. Data may be shared with researchers/institutions in countries within the EU where the AVG (Algemene Verordening Gegevensbescherming) applies. We will only share data with researchers/institutions in countries outside the EU, where the AVG does not apply, if we can ensure that the data can be shared securely and protected appropriately in accordance with the AVG. When this is not possible, we are not able to share the data outside of the EU. Participants have provided consent for the reuse of their anonymised data for scientific purposes. Data sharing is done using the Radboud research data repository (http://data.donders.ru.nl) in accordance with institutional, Radboud University, and EU guidelines. We will share only anonymised behavioural data, and anonymised (derived) (f)MRI data through a managed access format (users will submit a brief research proposal and which variables are needed to conduct the relevant analyses). Raw (f)MRI files cannot be not shared externally. Collected data for this project is stored in digitised data archives, maintained by the IT department of the Donders Institute.

## Abbreviations

ADHD: Attention-deficit/hyperactivity disorder
ASD: Autism spectrum disorder
BOLD: Blood oxygen level-dependent
BRIEF-2: Behaviour Rating Inventory of Executive Function 2
CODEC: COgnitive Dynamics in Early Childhood
DCCN: Donders Centre for Cognitive Neuroimaging
DSEM: Dynamic Structural Equation Modelling
FA: Fractional anisotropy
fMRI: Functional magnetic resonance imaging
HSC: Highly Sensitive Child scale
ICV: Coefficient of variation
iSD: Individual standard deviations
MaRs-IB: Matrix Reasoning Item Bank
MEWS: Mind Excessively Wandering Scale
SDQ: Strengths and Difficulties Questionnaire
SEM: Structural Equation Modelling
SES: Socio-economic status
SOPs: Standardised operating procedures
